#### Kinematic data analysis

The upper limb model of the University of Western Australia (UWA) will be applied to the 3D motion analysis of the landmark motion analysis system. The model includes 18 markers; the trunk, upper arm, forearm, and hand segments are defined according to the location of anatomical markers. The calibration anatomical system technology is used to establish the markers related to the coordinate system of the upper arm group or the forearm group. The movement of the upper limb landmarks can be reconstructed from their position relative to the upper limb technical coordinate system. The 3D coordinates of the anatomical markers recognized from the Kinect system bone model are recorded during the task. Local segment coordinates are established, including the torso and upper arm; each segment coordinate is based on global coordinates.

Azure Kinect SDK2.0 and Microsoft Visual Studio 2016 will be used to save the kinematic data and time range. The 3D position data collected by the Kinect sensor will be imported into MATLAB 2018a and then processed using a method previously developed by the research team to establish the kinematics model of Azure Kinect. Azure Kinect can measure XYZ coordinate data of 25 joints of the body. Kinematic data of 10 joints, including the spine, left and right shoulder, left and right elbow, left and right wrist, and left and right hand, will be used. Each repetition segments the original data and is then filtered by singular spectrum analysis (SSA) to reduce the impact of noise. The analysis calculates the kinematic index according to the filtered data. For the Kinect upper limb evaluation system, the measured node space position is used as the input, and the developed markerless motion analysis system calculates the joint angle and space-time parameters. A Butterworth low-pass filter with a cut-off frequency of 6 Hz is used. Then, the customized upper limb kinematics calculates the three Euler angles of shoulder rotation for the Azure Kinect system, which follow the sequence of flexion (+)/extension (−), adduction (+)/abduction (−), and internal rotation (+)/external rotation (−). Elbow flexion is calculated using trigonometric functions from the position data of ShoulderRight, ElbowRight, and WristRight.

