#### Inclusion criteria

To be eligible to participate in the study, each participant must meet the following criteria:Meet the diagnostic criteria of ‘stroke’ in the diagnostic essentials of various cerebrovascular diseases adopted at the Fourth National Cerebrovascular Disease Academic Conference in 1995 and confirmed by head computed tomography or magnetic resonance imaging;The first stroke occurred between 2 weeks and 6 months prior to commencing the study;Unilateral cortical lesion (left or right hemisphere) or subcortical lesion involving the motor pathway;The muscle strength of the upper limb of the affected side is ≥ 3 and muscle tone is ≤ 2 based on the Modified Ashworth Scale (MAS);Right-handedness before stroke;Age between 50 and 70 years;Blood pressure stable and below 160/100 mmHg;A Mini-Mental State Examination (MMSE) score of > 17 points for illiterate participants, > 20 points for participants with a primary school education, and > 24 points for participants with a middle school and above education;Brunnstrom stage ≥ IV in the affected upper limb;Standing balance ≥ level 2, the ability to stand independently for more than 5 min, and the ability to walk independently for more than 6 m;Willing to sign the informed consent form and understand, accept, and implement the rehabilitation guidance.

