#### Secondary outcome measures

Kinematic analysis includes endpoint performance parameters, joint angle, shoulder/elbow coordination index, and trunk compensatory motion. Two Kinect motion capture systems will be used for a kinematic evaluation to analyse the three-dimensional motion of the trunk and upper limbs while reach-to-grasp-pen and Tai Chi Cloud Hand. During the measurement process, the camera unit with high spatial resolution immediately calculates the three-dimensional (3D) coordinates of the mark. The Kinect SDK automatically collects data. The captured data are transferred to MATLAB software for customized analysis. Azure Kinect records XYZ coordinate data of 25 anatomical landmarks at a sampling frequency of 30 Hz. These landmarks, which do not require markers, include the head, neck, spine, left and right shoulders, left and right elbows, left and right wrists, left and right hands, left and right fingertips, left and right thumbs, middle ridges, left and right hips, left and right knees, left and right ankles, and left and right feet. To ensure stable mark recording, Azure Kinect is placed on a tripod with a height of 114 cm, an inclination angle of 20°, and a distance of 140 cm from the far end of the table. The table and chair are 75 cm and 46 cm high, respectively. The participant sits comfortably on the chair in front of Kinect and naturally completes the tasks of reach-to-grasp-pen with their upper limbs and Tai Chi Cloud Hand at their own pace. The participant is encouraged to follow the guidance video and repeat each task five times. No additional assistance is provided to the subjects unless there are safety issues.

The Modified Ashworth Scale (MAS) will be used to evaluate the change in passive motor resistance and spasm [38]. This 6-point sequential scale will be used to measure tone in the scapular adductor, elbow, wrist, and finger flexors at rest; the score ranges from 0 (muscle tension does not increase) to 4 (the affected part is stiff during flexion or extension). A MAS score of ≥ 1 in one or more muscles indicates a spasm.

The Wolf Motor Function Test (WMFT) will be used to evaluate the functional activity of the upper limbs [39]. The WMFT consists of 15 items. Items 1–6 are simple joint movements while items 7–15 are compound functional movements. The WMFT score is determined based on the quality of all actions (0–5 points, six grades).

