Effective connectivity (EC) analysis of the CLN is based on defining brain and muscle regions and ROIs. The basis for extracting ROIs from brain regions is that the brain map guides ROIs, and there are no overlapping regions to ensure the selection of functionally meaningful connected regions. The cortical reconstruction of the head model is used as the accurate geometric head model of the subjects. The EEG signals collected from the standard electrode leads of the international 10–20 system are represented on an accurate geometric model. First, the motor areas of the unaffected and affected sides are selected as ROIs, defined as Mu and Ma, respectively. The unaffected and affected somatosensory cortices are also considered to be ROIs, corresponding to Su and Sa, respectively. Finally, ROIs from unaffected and affected frontal and parietal regions are defined as Fu, FA, PAu, and PAa, respectively. For the muscle regions related to the two anatomical parts of the upper limb, according to the signals collected from the myoelectric electrodes on the affected side, the proximal (including the superior trapezius, the anterior deltoid, the posterior deltoid, the middle deltoid, the biceps brachii and the triceps brachii) and distal muscles (including the flexor carpi radialis and the extensor carpi radialis longus) of the upper limb are divided into two regions, which are defined as PM and DM. Based on the above 14 ROIs, the inflow index (IFI) and the outflow index (OFI) are used to determine the causal relationship between ROIs before and after training. To determine the difference in the average FcePDC value between the two groups in each frequency band before and after training, the FcePDC value calculated before training is defined as the baseline. The baseline changes are calculated by subtracting the baseline before training from the post-training values, and an independent-sample two-tailed *t*-test is performed to compare the changes between the two groups. In addition, repeated measures analysis of variance is used to test the statistical difference in the average FcePDC values in different information flow directions before and after training. Bonferroni correction is used to correct for multiple comparisons. The inter-group differences in network parameters (weighted clustering coefficient [C_W_] and weighted shortest path length [L_W_]) are tested with the Mann-Whitney *U* test. For EC analysis, the IFI and OFI values of ROI changes before and after training in the two groups are tested by paired two-tailed *t*-tests. The consistently paired *t*-test is used for the betweenness centrality parameter (BCX). The confidence level *α* is defined as 0.05.

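### Elbow flexion is defined from right-arm landmarks only, although the left arm may be the affected one; the rule should name the affected side

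*Protocol article*

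**What the plan says.** The Kinematic data analysis section of the protocol article gives one rule for the elbow angle: "Elbow flexion is calculated using trigonometric functions from the position data of ShoulderRight, ElbowRight, and WristRight". It sets no condition on the affected side and offers no left-sided counterpart. Earlier in the same section, the list of joints whose data are processed covers both sides: "left and right shoulder, left and right elbow, left and right wrist, and left and right hand, will be used".

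The Inclusion criteria allow either side to be affected: "Unilateral cortical lesion (left or right hemisphere) or subcortical lesion involving the motor pathway". Motor stage is judged on whichever limb is paretic ("Brunnstrom stage ≥ IV in the affected upper limb"). Participants must also meet "Right-handedness before stroke".

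Under Secondary outcome measures, the elbow angle falls within a named outcome: "Kinematic analysis includes endpoint performance parameters, joint angle, shoulder/elbow coordination index, and trunk compensatory motion". In the recorded tasks the participant "naturally completes the tasks of reach-to-grasp-pen with their upper limbs and Tai Chi Cloud Hand at their own pace"; no side is named.

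In Analysis of fNIRS, EEG, and EMG data, by contrast, the muscle regions are defined "according to the signals collected from the myoelectric electrodes on the affected side".

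**The concern.** The kinematic measures are meant to show whether the impaired arm regains normal movement or compensates; the Background gives this as their purpose. An elbow angle from the healthy arm cannot show that. If the rule is coded as printed, the group comparison for elbow flexion pools affected elbows in right-arm-affected participants with unaffected elbows in left-arm-affected ones. Any effect of Tai Chi on the affected elbow would then be averaged with whatever happens in the healthy elbow, and the estimate would have no clear clinical meaning. A null result could reflect the definition and not the treatment.

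**Working it through.** The plan states no figure on this point, so the check is mainly textual.

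**Which elbow the rule measures.** A unilateral lesion affects the opposite arm, so eligibility produces two cases:

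| Lesion | Affected arm | Arm in the rule | Elbow angle comes from |
|---|---|---|---|
| Left hemisphere | Right | Right | Affected arm |
| Right hemisphere | Left | Right | Unaffected arm |

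**Whether other text resolves it.**
- The handedness criterion fixes dominance before the stroke, not the side of paresis.
- The task description does not confine the movement to one arm.
- The list of joints includes the left elbow, but it names inputs. The definition that follows uses none of the left-side ones.
- The affected-side wording for the muscle regions applies to the EMG signals. The kinematic section has no equivalent.

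**Which components are touched.**
- Elbow flexion: explicitly tied to right-side landmarks.
- Shoulder/elbow coordination index: no formula is given, so it is touched only if it uses this angle.
- Endpoint parameters, shoulder angles, trunk compensation: not stated to be right-only.
- FMA-UE, the primary outcome: not derived from these data.

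**Size of the dilution.** Let f be the share of participants whose left arm is affected, δA the treatment effect on change in the affected elbow and δU the effect in the unaffected elbow. With f equal in expectation in both groups,

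measured effect = (1 − f) × δA + f × δU.

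The documents give none of these three quantities. With 84 participants and δU = 0 (assumption):

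| f (assumed) | Unaffected elbow measured (84 × f) | Share of δA retained (1 − f) |
|---|---|---|
| 0.3 | 25.2, about 25 | 70% |
| 0.5 | 42 | 50% |
| 0.7 | 58.8, about 59 | 30% |

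If the healthy elbow also benefits, less is lost. With f = 0.5 and δU = 0.5 × δA (assumption), the measured effect is 0.5 × δA + 0.5 × 0.5 × δA = 0.75 × δA.

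**The case against.** The best defence is that the right-side names only illustrate the landmark triplet. The section says that both elbows' data are used, which would be hard to explain if the left elbow never entered a calculation. The article is condensed, and the processing follows a method developed earlier by the team that is not shown. The working script may already select the correct arm.

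This stands in part. It means nobody can say from the article that the wrong elbow has been or will be measured, and that the fault may lie only in the wording. It does not rescue the sentence, which is a stated rule and not an omitted detail. Nothing marks it as an example, and a programmer following it would code the right arm.

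Four stronger readings are tempting, but the documents do not support them.
- *A reader might infer that the whole kinematic outcome is on the wrong side.* Only elbow flexion is tied to right-side names.
- *A reader might infer that the shoulder-angle signs also go wrong unless the left side is mirrored.* The signs are given by anatomical direction (flexion, adduction, internal rotation), which is defined relative to the limb. No unmirrored calculation is described.
- *A reader might infer a specific loss of power.* Borrowing the FMA-UE planning effect of 0.683, with δU = 0, equal SDs in both arms and f = 0.5, power at 42 per group falls from about 0.88 to about 0.35 by the normal approximation. But the plan claims no power for any kinematic outcome, and nothing says that this effect size applies to elbow flexion.
- *A reader might infer that chance imbalance in lesion side biases the comparison.* The Abstract defines the secondary outcomes as mean changes, so stable differences in level between sides cancel. What remains is differing change between affected and unaffected elbows; under randomization that is noise, not systematic bias.

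**Conclusion.** The point holds for elbow flexion. The only definition in the article is right-sided and unconditional. It conflicts with eligibility for lesions of either hemisphere and sits badly with the same section's statement that both elbows are used. As written, it gives the unaffected elbow in every left-arm-affected participant. Extension to the coordination index is an inference.

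The consequence is dilution of any effect on this component. Its size depends on the left-affected share and on how far the healthy elbow responds, neither of which the documents give, so the figures above show only the form of the loss. The textual conflict does not depend on them. This is a correctable fault in one component of a secondary outcome and does not threaten the trial's primary result.

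**What to change.** Replace the sentence with, for example: *Elbow flexion, and any index derived from it, is computed from the shoulder, elbow and wrist landmarks of the affected side; the same quantities for the unaffected side are reported separately.* If elbow flexion is the angle formed at the elbow by the three landmarks, it is unchanged by reflection, so choosing the left or right triplet is enough.

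Confirm that the MATLAB script selects the side from each participant's recorded affected arm, and reprocess existing recordings if it does not. Do this before the first unblinding step in the Blinding section, and before any interim look at kinematic data by group label. The choice of arm then cannot be influenced by results.

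The cost is one sentence, a check of the script and possibly a rerun. Landmarks on both sides are already recorded, so no new data are required.

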#### Analysis of fNIRS, EEG, and EMG data

For data pre-processing, a notch filter first filters the original EEG signal at a frequency of 50 Hz to eliminate power line noise, followed by a fourth-order Butterworth bandpass filter (0.5–45 Hz). Independent component analysis is used to remove eye movement artifacts. The data are re-referenced by subtracting the average of all channels from each channel. Subsequently, the EEG data are subdivided into multiple tests. These tests start from 500 ms before the tasks and last to 3000 ms after the baseline, and each test is corrected. Finally, any test with artifacts is manually checked and excluded. For fNIRS signals, a fourth-order Butterworth bandpass filter (0.01–0.5 Hz) is applied to eliminate artifacts, such as cardiac interference (0.8 Hz). Then, the wavelet-based method removes the motion artifacts from the fNIRS signal. The changes in haemoglobin (HbO) and deoxygenated haemoglobin (HbR) concentrations are calculated according to the modified Beer-Lambert law. The signals obtained from each channel are checked manually, and noisy tests are excluded from further analysis. A general linear model is used to identify activation channels that are significantly induced by each hand motion. These channels are used as a spatial prior for EEG source imaging.

Functional connectivity analysis is based on graph theory. Theoretically, the network can be represented by a graph composed of vertices and corresponding edges. From the perspective of the CLN framework, through the network method based on weighted graph theory and considering the edge strength of the FC CLN, the dynamic changes in cortical-muscular-cortical coordinated working mode before and after Tai Chi are characterized. Specifically, the correlation matrix between different electrode signals is established to define the corresponding weights. The matrix coefficients are taken as Wxy and link the X and Y points. FcePDC is used as the value. The FcePDC value of the matrix in the EEG-EEG, EEG-EMG, and EMG-EMG channel pairings of 40 vertex networks (40 EEG and 8 EMG) is used as the edge weight. Based on weighted graph theory, three global matrices are used to measure the network characteristics. The small world measurement of the network—that is, the weighted clustering coefficient and the weighted shortest path—is used to quantitatively evaluate the local efficiency of information transmission and the ability of parallel information transmission in the network. In addition, the betweenness centrality is used to analyse the regional characteristics in CLN.

Effective connectivity (EC) analysis of the CLN is based on defining brain and muscle regions and ROIs. The basis for extracting ROIs from brain regions is that the brain map guides ROIs, and there are no overlapping regions to ensure the selection of functionally meaningful connected regions. The cortical reconstruction of the head model is used as the accurate geometric head model of the subjects. The EEG signals collected from the standard electrode leads of the international 10–20 system are represented on an accurate geometric model. First, the motor areas of the unaffected and affected sides are selected as ROIs, defined as Mu and Ma, respectively. The unaffected and affected somatosensory cortices are also considered to be ROIs, corresponding to Su and Sa, respectively. Finally, ROIs from unaffected and affected frontal and parietal regions are defined as Fu, FA, PAu, and PAa, respectively. For the muscle regions related to the two anatomical parts of the upper limb, according to the signals collected from the myoelectric electrodes on the affected side, the proximal (including the superior trapezius, the anterior deltoid, the posterior deltoid, the middle deltoid, the biceps brachii and the triceps brachii) and distal muscles (including the flexor carpi radialis and the extensor carpi radialis longus) of the upper limb are divided into two regions, which are defined as PM and DM. Based on the above 14 ROIs, the inflow index (IFI) and the outflow index (OFI) are used to determine the causal relationship between ROIs before and after training. To determine the difference in the average FcePDC value between the two groups in each frequency band before and after training, the FcePDC value calculated before training is defined as the baseline. The baseline changes are calculated by subtracting the baseline before training from the post-training values, and an independent-sample two-tailed *t*-test is performed to compare the changes between the two groups. In addition, repeated measures analysis of variance is used to test the statistical difference in the average FcePDC values in different information flow directions before and after training. Bonferroni correction is used to correct for multiple comparisons. The inter-group differences in network parameters (weighted clustering coefficient [C_W_] and weighted shortest path length [L_W_]) are tested with the Mann-Whitney *U* test. For EC analysis, the IFI and OFI values of ROI changes before and after training in the two groups are tested by paired two-tailed *t*-tests. The consistently paired *t*-test is used for the betweenness centrality parameter (BCX). The confidence level *α* is defined as 0.05.

Correlation analysis will also be employed. For the above brain functional features (based on brain imaging and graph theory analysis), brain regions with significant differences between groups are selected and relevant eigenvalues are extracted. The eigenvalues of functional brain connections of brain regions with significant differences or the partial and factor correlations between the eigenvalues of functional brain connections and upper limb scores are determined. Moreover, the factors that have the most significant impact on the cortex are analysed. The results are controlled for the influence of age, gender, education level, and other factors. Because the trial uses a single-blind design, the statisticians will conduct an interim analysis according to the label but without unblinding to guide the follow-up study.

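### The small-world measures are compared between groups without normalisation, so L_W (and C_W under some definitions) can differ because overall coupling differs while network organisation is unchanged

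*Protocol article*

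**What the plan says.** All of the following stands in the Protocol article, Statistical analyses, under Analysis of fNIRS, EEG, and EMG data, unless another section is named.

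- **Edge weight.** "The matrix coefficients are taken as Wxy and link the X and Y points. FcePDC is used as the value". For EEG-EEG, EEG-EMG and EMG-EMG pairs, the FcePDC of the "channel pairings of 40 vertex networks (40 EEG and 8 EMG) is used as the edge weight".
- **Definition of the measure.** "The small world measurement of the network—that is, the weighted clustering coefficient and the weighted shortest path".
- **Meaning given to it.** The pair, "the weighted clustering coefficient and the weighted shortest path—is used to quantitatively evaluate the local efficiency of information transmission"; capacity for parallel transmission is named as well.
- **Test.** "The inter-group differences in network parameters (weighted clustering coefficient [C_W_] and weighted shortest path length [L_W_]) are tested with the Mann-Whitney" U test.
- **Mean coupling.** The same section separately compares the change in average FcePDC between the two groups, by frequency band, with an independent-sample t-test.
- **Status.** Exploratory outcomes measures lists clustering, shortest path and betweenness centrality among the exploratory results.

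The article names no random or surrogate reference network, no rescaling of the weights and no adjustment for mean FcePDC. It does not say how a weight becomes a path length, or which weighted clustering coefficient is meant.

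**The concern.** Whether a network is small-world is a relative question: are clustering and path length high or low compared with a random network of the same size and the same weights? The article equates the small-world measure with C_W and L_W themselves and takes them straight to a between-group test. A path length built from edge weights carries the scale of those weights. If every FcePDC value rises by the same factor, the pattern of connections is unchanged, but L_W moves.

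The Background gives the purpose of the graph analysis as explaining how the cortical-muscular network reorganises under Tai Chi. If Tai Chi raised coupling generally, or if signal quality differed between groups, unnormalised L_W could differ with no reorganisation at all, and the result could be reported as reorganisation. The last part of the analysis section also takes features that differ between groups, including those from graph analysis, into correlations with upper limb scores. A misread measure could carry forward there.

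**Working it through.** The article gives no figure on this point, so there is none to reproduce. The check asks what happens to C_W and L_W when every weight is multiplied by k = 1.2 and nothing else changes.

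**Inputs.** From the article: edge weight w = FcePDC, and the network size. The article calls the networks 40-vertex but lists 40 EEG and 8 EMG vertices, which add to 48, so both sizes were run. Assumed: k = 1.2, and dense directed networks with weights drawn as 0.8 × Beta(2, 8), 20 networks at each size.

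**Path length.** L_W is the mean over vertex pairs of the smallest sum of edge lengths along a path.

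- Length = w: every path is multiplied by k, so L_W changes by 1.2 − 1 = +20.0%.
- Length = 1/w: every path is divided by k, so L_W changes by 1/1.2 − 1 = 0.833 − 1 = −16.7%.
- Length = −log w: every edge shortens by log 1.2 = 0.182, so L_W falls. Simulated: −13.5% (40 vertices) and −13.8% (48).
- Length = 1 − w: every edge shortens by 0.2w, so L_W falls. Simulated: −3.8% at both sizes.

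The first two results are exact for any set of weights. The last two depend on the assumed distribution.

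**Clustering.**

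| Weighted definition | Effect of k | Change in C_W |
|---|---|---|
| Geometric mean of triangle weights, unscaled | (k³)^(1/3) = k | +20.0% |
| Same, weights divided by their maximum | k cancels | 0.0% |
| Barrat form | k cancels between weights and strengths | 0.0% |
| Zhang form, weights divided by their maximum | k cancels | 0.0% |

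So C_W responds to a uniform change under some definitions only.

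**Ratio to random networks.** Shuffle the weights of the same matrix among its edges, recompute the measure and divide. The shuffled networks carry the same factor k, so for 1/w lengths the ratio is (L_W/k) ÷ (L_random/k) = L_W ÷ L_random. For unscaled geometric-mean clustering it is (k·C_W) ÷ (k·C_random) = C_W ÷ C_random. Simulated change: 0.0% for both measures at both sizes.

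**Betweenness.** With 1/w lengths a common factor does not alter which path is shortest, so betweenness centrality does not move in this check.

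**The case against.** The strongest reply has three parts.

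1. **Missing detail.** A journal article may leave the length map, the clustering formula and any normalisation to a fuller plan. For the first two this stands, and their absence is not the point here. Normalisation is less easily set aside, because the article states what the small-world measure is and names the test applied to it, and neither statement leaves a place for a reference network.

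2. **A stylised check.** Multiplying all weights by one constant is a limiting case, and real training effects would be uneven. This also stands in part. The check shows that L_W can move with no reorganisation. It does not show that C_W and L_W merely repeat the average-FcePDC test, and that should not be claimed.

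3. **Exploratory status.** No confirmatory conclusion depends on these measures. This stands and sets the severity.

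Two stronger readings are tempting. A reader might infer that, because FcePDC "is used as the edge weight", shortest paths run through the weakest links, so that L_W has the wrong sign and betweenness marks hubs of weak coupling. That requires raw FcePDC to be summed as distance, which the article never says. It treats the weight as a strength, and converting strength to length by an inverse map is the usual step. All three inverse maps tried move L_W in the expected direction. A reader might also infer that both measures necessarily follow mean coupling. Three of the four clustering forms tried do not, and the article does not say which it uses.

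**Conclusion.** The point holds in a limited form. As defined and tested in the article, L_W changes with overall FcePDC strength under every length map tried, and C_W does so under some definitions. For a uniform 20% rise in FcePDC, L_W changes by −16.7% with 1/FcePDC lengths, with organisation unchanged. Across the three inverse maps the fall runs from 3.8% to 16.7%, and the two smaller figures rest on assumed weights. A between-group difference in these measures cannot, on its own, be separated from the difference in mean coupling that the same section already tests. The 0.0% change after normalisation was shown for 1/w lengths and unscaled geometric-mean clustering.

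The documents do not support a claim that L_W has the wrong sign or that betweenness identifies weak hubs. Severity is low: the outcomes are exploratory and the FMA-UE analysis is untouched.

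**What to change.** In the functional connectivity part of the analysis section:

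- State an inverse weight-to-length map, such as 1/FcePDC, for the shortest path and for betweenness centrality, and name the clustering definition.
- For each participant at each visit, divide C_W and L_W by their means over weight-preserving random networks built from that participant's own matrix.
- Apply the between-group test to these ratios and base any statement on small-world organisation or reorganisation on them. Report the raw values alongside.
- Leave overall coupling strength to the existing comparison of average FcePDC.

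The cost is analysis code and some computing time for the random networks. No new data, visits or participants are needed. The normalised ratios may show smaller between-group differences than the raw measures.
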